# TOB-STOP-COP (TOBacco STOP in COPd trial): study protocol—a randomized open-label, superiority, multicenter, two-arm intervention study of the effect of “high-intensity” vs. “low-intensity” smoking cessation intervention in active smokers with chronic obstructive pulmonary disease

**DOI:** 10.1186/s13063-020-04653-z

**Published:** 2020-08-21

**Keywords:** COPD, Randomized controlled trial, Smoking cessation, Exacerbations, Varenicline

## Abstract

**Background:**

Cigarette smoking is the leading cause of chronic obstructive pulmonary disease (COPD), and it contributes to the development of many other serious diseases. Smoking cessation in COPD patients is known to improve survival and reduce the number of hospitalization-requiring acute exacerbations of COPD. However, smoking cessation interventions in these patients have only been successful for approximately 15–20% for consistent smoking abstinence in 12 months. Thus, more effective interventions are needed for this patient group. The aim of this study is to determine whether a high-intensity intervention compared to a low-intensity intervention can increase the proportion of persistent (> 12 months) anamnestic and biochemical smoking cessation in active smokers with COPD.

**Methods:**

This study is a randomized controlled trial. A total of 600 active smokers with COPD will be randomly assigned 1:1 to either a standard treatment (guideline-based municipal smoking cessation program, “low intensity” group) or an intervention (“high-intensity” group) group, which consists of group sessions, telephone consultations, behavior design, hotline, and “buddy-matching” (smoker matched with COPD patient who has ceased smoking). Both groups will receive pharmacological smoking cessation. The primary endpoint is anamnestic and biochemical (cotinine analysis in urine) validated smoking cessation after 12 months.

**Discussion:**

The potential benefit of this project is to improve smoking cessation rates and thereby reduce smoking-related exacerbations of COPD. In addition, the project can potentially benefit from increasing the quality of life and longevity of COPD patients and reducing the risk of other smoking-related diseases.

**Trial registration:**

ClinicalTrials.gov NCT04088942. Registered on 13 September 2019

## Background

COPD is a life-threatening and incurable lung disease characterized by persistent breathing problems and poor airflow in the lungs that usually worsens over time. Globally, it is estimated that 250 million people have COPD and that three million deaths annually, corresponding to 5% of all deaths, are caused by COPD [1]. In Denmark, COPD is the third most common cause of death, as it contributes to 5500 deaths a year [2]. Cigarette smoking is by far the most important cause of COPD by damaging the alveolar sacs (the tar and gas phases of cigarette smoking contain high concentrations of free radicals, leading to oxidative stress and inflammation [3]). Cigarette smokers have a higher incidence of respiratory symptoms and abnormal lung functions, a greater annual decline in FEV_1_ (forced expiratory volume in 1 s) and a greater mortality rate than non-smokers [4]. Other types of tobacco, e.g., pipes, cigar, hookahs, are also risk factors for the development of COPD [4, 5] as well as passive exposure to cigarette smoke (passive smoking) by increasing the overall burden on the lungs of inhaled particles and gasses [4].

Acute exacerbation of COPD is a worsening of the patient’s respiratory symptoms, such as shortness of breath and cough that lasts for several days, and requires medical treatment beyond the patient’s usual medicine. Exacerbations of COPD can be caused by tobacco smoking [6] and are associated with increased risk of mortality due to decreasing lung function and activity level and often lead to hospitalization [7, 8]. This is one of the biggest costs for the healthcare system for the treatment of COPD [9]. In addition, there is evidence that exacerbations of COPD increase the risk of myocardial infarction [10] and strokes [11]. Tobacco smoking in patients with COPD can also contribute to other comorbidities such as lung cancer (both with regard to individual and population risk [12]) that can contribute to the poorer overall health and increased risk of mortality. The individual risk of lung cancer increases with an increasing number of cigarettes smoked per day and the duration of years of smoking, and the population risk increases with the incidence of current smokers [12].

In this way, smoking cessation will be the most effective intervention to stop the development of COPD, lessen the aforementioned risks associated with tobacco smoking, and increase survival and reduce morbidity [13]. Overall, tobacco smoking thus increases mortality and serious morbidity as well as symptoms in COPD patients, and smoking cessation should be the top priority in treating COPD.

### Current evidence of smoking cessation

There are a number of approaches for treating tobacco dependence, including behavioral therapy and pharmacotherapy, but smoking cessation is only successful in a proportion of patients with COPD, especially on a long-term basis [14, 15].

A Cochrane review from 2016 (16 studies, involving 13,123 smokers with COPD) shows among other things, from two studies, sublingual nicotine tablets and varenicline increased smoking cessation rates compared to placebo over twice as much, respectively, RR 2.60 (95% CI 1.29–5.24) and RR 3.34 (95% CI 1.88–5.92) [16]. Pooled results from two other studies also showed a positive effect of bupropion compared to placebo (RR 2.03 (95% CI 1.26–3.28)) [16]. By combining these four studies, there was high-quality evidence for the effect of pharmacotherapy plus high-intensity behavioral therapy compared to placebo plus high-intensity behavior therapy (RR 2.53 (95% CI 1.83–3.50)) [16].

In a study from 2008, smoking cessation rates were examined in a group of patients with COPD who participated in a 1-year smoking cessation program (*N* = 247) and were compared with a group of COPD patients who received normal care (*N* = 231) with follow-up 1 year and 3 years after starting the program [17]. The smoking cessation program included a 2-week period of admission to hospitals, group sessions where NRT and exercise were recommended/advised in, and in addition telephone calls with specially trained staff who gave feedback and support for smoking cessation throughout the year [17]. In the smoking cessation program, 52% of patients ceased smoking after 1 year and 38% after 3 years, correspondingly in the normal care group 7% after 1 year and 10% after 3 years [17]. However, the study is not in a controlled design, but the results are still inspiring.

Although many different methods of smoking cessation and several years of preventive action have been tried, they have all had very little effect. And this despite the many known harmful effects of continued smoking. Thus, more effective interventions are needed for this patient group.

The hypothesis in the study described here is that a person-adapted, multi-component, intensive smoking cessation intervention results in a higher incidence of anamnestic and biochemical smoking cessation after 12 months in people diagnosed with COPD and (as the last 8 weeks before inclusion in the study) are current daily smokers than a standard smoking cessation intervention with municipal smoking cessation offers and offers of varenicline.

## Methods

### Design

This is a randomized open-label, superiority, multicenter, 2-arm intervention study, in which it is examined if a “high-intensity” intervention causes fewer people (diagnosed with COPD) to smoke after 12 months than in a “low-intensity” intervention in people diagnosed with COPD. The effect on survival for 12, 24, and 48 months; incidence of COPD exacerbations; number of admissions for all causes; and cardiovascular admissions will also be analyzed at the same time.

Additionally, a few sub-studies will be conducted:
Sub-study 1: We will examine the prevalence of depression/anxiety within 36 months in the “high-intensity” and “low-intensity” groups by means of questionnaires, by hospital admissions, and by recording the prescription of drugs for depression and anxiety.Sub-study 2: In a subset of patients who quit smoking from the “high-intensity” group (*n* = 50) and patients who do not quit smoking from the “low-intensity” group (*n* = 50), we are going to examine the potential changes in the respiratory microbiome within 6 months of smoking cessation attempt.

### Recruitment and inclusion

Recruitment takes place through advertisements and announcements in local newspapers, daily newspapers, via the Danish Lung Association and its member magazine, where the participants then per mail or telephone can contact trial staff (see under the “Data collection” section) and then receive the written participant information per mail or other ways if the participant wants this. Later, an information meeting with trial staff can be agreed on one of the participating departments’ cadastre, in a booked room that is approved for patient examination. The participant will be informed of the right to an assessor in the first contact, and the right will also be clarified in the written participant information. For the meeting, oral participant information will be provided by trial staff, and the aim is to ensure that trial staff do not have work during the recruitment and if they have, the work telephone is handed over to other staff during the meeting. After the meeting, a 24-h reflection period will be given, and informed consent will be obtained upon the signed consent declaration, provided that the participant will participate in the project.

The inclusion criteria are as follows:
Age ≥ 50 yearsCompetent and capableHave diagnosed COPD [*spirometry verified and evaluated by pulmonary specialist*]Current daily smoker [*minimum 1 cigarette daily*]Have smoked minimum 20 pack-years (1 pack-year = 20 cigarettes daily in 1 year)Want to or try to stop smokingDo not mind taking varenicline or NRT during the trialAre willing to give blood and urine samples according to the protocol

The exclusion criteria are as follows:
Previously included in the trialHospitalized with COPD exacerbation within the last 24 monthsAre associated with hospital outpatient clinic for COPD disease treatmentHave FEV_1_ < 50%.Pregnancy/breastfeedingLife expectancy less than 1 yearSevere linguistic problems or inability to give informed consentSevere mental illness that is not controlled with medicationActive alcohol or substance abuseActive cancer disease*

*The person can participate if he or she has had a cancer disease that is now referred to as curative/radically treated. Basal cell carcinoma of the skin does not count as an exclusion criterion.

### Interventions

A total of 600 participants will be included with start-up 1 January 2020 and is expected to be completed 3 years later, January 2023. Participants are randomized (random allocation) 1:1 to a “low-intensity group” and a “high-intensity group,” stratified for age (> 65 years vs. ≤ 65 years) and number of daily cigarettes (> 10/day vs. ≤ 10/day), and blocked randomization through REDCap with blocks of varying sizes (4–8), which will not be disclosed. Participants, their data, and laboratory specimens will be assigned a coded identification number, ID, to maintain participant confidentiality. Offers of varenicline are the standard municipal smoking cessation intervention and thus our choice of comparator. Participants will be randomized to one of the following:
“Low-intensity group”: encouraged to quit smoking via own GP and varenicline is prescribed for 12 weeks. Encouraged to only adhere to this “low-intensity” intervention.“High-intensity group”:
Varenicline for 12 weeksGroup sessions—in all 30 sessions divided into 6 months
i.Preparation phase*: 5 sessionsii.Days 1–14: 5 sessionsiii.Days 15–30: 5 sessionsiv.Days 31–60: 5 sessionsv.Days 61–90: 5 sessionsvi.Days 90–180: 5 sessions

*During the preparation phase, participants are allowed to smoke; smoking cessation starts at day 1.

Group sessions are controlled by the following:
I.Respiratory nurse [mapping of different smoking patterns and different reasons for smoking. When is smoking the greatest? When in the process, smoking starts to fall. Dangerous situations regarding smoking relapses. Working closely with psychologist—see below. Initial focus on nicotine-craving and coping methods]II.Respiratory physician [lung function, lung age, anatomy, physiology, pathophysiology of lung cancer, and COPD]. Focus on why smoking cessation is good. Is there anything you want to experience in your life that smoking can prevent? Either by death or because illness would prevent it?III.Psychologist [in close cooperation with the nurse. Focus on behavior before smoking and how this behavior is slowed down at an early stage. Coping by smoking. Cognitive smoking cessation strategies. Handle digito-oral habit].IV.Physiotherapist [training on how to improve general physical performance status based on individual training programs].V.Dietician (focus on keeping weight (both ways), nutrition). Suggestions for what to eat at episodes of smoking craving.
(c)Relationships and retention via these:
i.A hotline is established which the “high-intensity group” can call.ii.Weekly calls to all participants in the project for 26 weeks, reminding of adherence. If the participant has not had a relapse, there will be calls at week 34 and week 42. If the participant has had a relapse, calls continue until relapse-free for 10 weeks, then week 34 and week 42.(d)“Buddy-arrangement”: participants who have completed the program and have become smoke-free are matched with new ones in the program. A meeting frequency of approx. every 7–14 days. The first participants are matched with outpatients from the COPD clinic who have ceased smoking.

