### Sample size (statistical power calculation)

Type 1 error limit (*α*) of 5%. Power (1-*β*) of 90%.

The maximum smoking cessation rate for the “low-intensity group” is expected to be 10% in 12 months. With the above-described person-adapted, multi-component, intensive smoking cessation intervention in the “high-intensity group”, ≥ 20% of participants are expected to cease tobacco smoking for at least 12 months. Thus, a 10% absolute improvement in the likelihood of smoking cessation is expected, in this case, equivalent to the relative risk of smoking cessation on 2.0. This gives a sample size of 532 (266 + 266) persons. To account for possible withdrawal from the study and lost to follow-up, 600 participants will be recruited for the project.

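### Centre is not a randomisation stratum, and neither centre nor the existing strata enter the stated primary comparison: a small forgone gain in precision, not a bias

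*Protocol article*

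**What the plan says.** The Design section of the protocol article states: "This is a randomized open-label, superiority, multicenter, 2-arm intervention study". The section on risks and adverse events also refers to further centres, but no number or size of centres is given.

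The Interventions section sets out the allocation: 1:1, "stratified for age (> 65 years vs. ≤ 65 years) and number of daily cigarettes" (above 10 v 10 or fewer per day), with "blocked randomization through REDCap with blocks of varying sizes (4–8), which will not be disclosed". Factors, cut-offs and block sizes are all given, and centre is not among the factors.

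The Analyses section gives the percentage of quitters per arm and compares the two arms by logistic regression. No covariate is named. Adjustment for baseline variables appears only in a later sentence about a Cox model, which does not list the variables.

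On delivery, the Interventions section lists five professions who run the high-intensity sessions and places low-intensity care with the participant's own GP. The abstract calls the comparator a "guideline-based municipal smoking cessation program". The article does not say whether each centre has its own session team, or whether comparator care differs between centres.

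**The concern.** The high-intensity arm is a programme of 30 group sessions with calls, a hotline and buddies, so its results may depend on who delivers it. If quit rates differ by centre and the split within centre is left to chance, part of the difference seen in a given trial reflects which centres happened to supply more participants to one arm. Three things could be at stake: bias, loss of planned power, or precision that a different analysis would recover. They need to be separated, because only the third proves to apply.

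A related point concerns the existing strata. Age and cigarettes per day were presumably chosen because they predict quitting. An unadjusted comparison after stratifying on prognostic factors tends to overstate the standard error, so part of the benefit of stratifying is lost. The article gives no quit rates by stratum, so this part cannot be sized.

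**Working it through.** **1. The plan's own figure.** Inputs from the Sample size section: 10% v 20%, alpha 5% (two-sided assumed), power 90%.

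n per arm = [1.960 × √(2 × 0.15 × 0.85) + 1.282 × √(0.10 × 0.90 + 0.20 × 0.80)]² / 0.10² = (0.990 + 0.641)² / 0.01 ≈ 266, so 532 in total. This matches the article. Power with 300 per arm is 93.1%.

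**2. How uneven a centre can become without a centre stratum.** Centre sizes are assumptions. For a centre of m among 600, the SD of (high minus low) is 2 × √[m × 0.25 × (1 − m/600)].

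- m = 200: 2 × √(50 × 0.667) = 11.5, so a 95% range of about ±23 (for example 111 v 89).
- m = 40: 2 × √(10 × 0.933) = 6.1, so about ±12 (for example 26 v 14).

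A simulation of the stated scheme (600 participants, four equal strata, blocks of 4, 6 or 8, 1,500 replicates per scenario) gave the worst centre's average departure from 50:50, in percentage points:

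| Equal-sized centres (assumed) | As stated | Centre added as stratum |
|---|---|---|
| 2 | 1.8 | 0.4 |
| 3 | 3.5 | 0.7 |
| 5 | 6.3 | 1.5 |
| 8 | 9.7 | 2.7 |

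**3. Effect on the risk difference.** With V the between-centre variance of quit rates, the SD of the arm difference due to centre mix is √(2V/300). Quit rates are assumptions.

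- Three centres of 200 at 8, 15 and 22%: V = (0.07² + 0 + 0.07²)/3 = 0.003267; SD = √(2 × 0.003267/300) = 0.47 points.
- Centres of 240, 160, 100, 60 and 40 at 8, 12, 15, 20 and 25%: size-weighted V = 0.002525; SD = √(2 × 0.002525/300) = 0.41 points.

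**4. Is this on top of the planned standard error?** No. The binomial variance at the overall rate is the average within-centre variance plus V. In the three-centre case, 0.15 × 0.85 = 0.1275, and (0.0736 + 0.1275 + 0.1716)/3 + 0.0033 = 0.1242 + 0.0033 = 0.1275. A sample size built on overall rates has already paid for V.

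The standard error of the risk difference is √(0.10 × 0.90/300 + 0.20 × 0.80/300) = 2.89 points. The removable share of variance is (0.47/2.89)² = 2.6% or (0.41/2.89)² = 2.0%.

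**5. Sensitivity.** The same simulation used quit rates spread around 15% (9.7 to 22.5%, or 7.3 to 28.2%). The chance difference averaged about zero, with an SD of 0.35 to 0.84 points. The share is then (0.35/2.89)² = 1.5% up to (0.84/2.89)² = 8.4%. The top value needs two centres whose quit rates differ almost fourfold. With centre as a stratum the SD fell to 0.07 to 0.14 points.

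Type I error of the unadjusted test was 3.9 to 6.5% without a centre stratum and 3.6 to 5.6% with one (Monte Carlo error about 0.6 points). The 6.5% arose with two centres and the narrower spread; the wider spread gave 4.9%. There is no consistent inflation.

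**The case against.** The strongest reply is that nothing here is wrong. Leaving centre out of the strata is a common and defensible choice, the sample size reproduces exactly, and power is not reduced. That stands.

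Second, the case for centre effects is an inference. The article mentions one hotline, draws the first buddies from a COPD clinic named in the singular, and says that staff tasks after allocation follow standard operating procedures. Low-intensity care sits with each participant's own GP, so its variation is mainly between participants, and a centre stratum would not balance it. That stands too: centre differences are possible, not documented.

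Third, model covariates are often left to the SAP, which is not shown. This stands in part. The SAP may already include them, and the point then shrinks to a check. But the article states the allocation factors in full and ties adjustment to a Cox model rather than to the primary logistic regression.

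Fourth, stratifying by centre has a price. A centre of 40 with four strata has about 10 participants per stratum, so blocks of 4 to 8 will often be left incomplete, and short local lists are easier to guess in an open-label trial. This stands, which is why the analysis comes first in the fix.

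A reader might go further and infer any of the following. The documents do not support them.

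- That centre differences bias the result: the imbalance is random, with mean zero.
- That they add variance beyond the plan: step 4 shows that they do not.
- That care is known to vary by centre: this is not stated.
- That one central list is used: the article names only REDCap.
- That small centres could not run their groups: neither group size nor centre size is given, and an exact 20/20 split would leave a centre of 40 no larger.

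**Conclusion.** The point holds as a minor one about precision. In a multicentre trial, balance within centre is left to chance, and the stated primary comparison uses neither centre nor the two factors on which randomisation is stratified. There is no bias in expectation, no consistent type I error inflation and no loss of the stated 90% power.

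What is forgone is about 2 to 3% of the variance of the risk difference under assumed centre quit rates of 8 to 25%, or 1.5 to 8.4% over the wider assumptions. The chance component has an SD below 1 point, against a planned effect of 10 points.

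This rests on assumed numbers, sizes and quit rates of centres, on 600 participants analysed, and on the listed strata being complete.

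**What to change.** **Analysis (main change).** State that the primary logistic regression includes arm, age group (> 65 v ≤ 65 years), cigarette group (> 10 v ≤ 10 per day) and centre. Very small centres should be pooled by a rule fixed before the arms are compared: a centre of 40 at 15% has only about 40 × 0.15 = 6 quitters. The adjusted odds ratio is conditional on these factors, so a risk difference standardised from the same model should accompany it, because the trial was sized on absolute rates. The cost is a sentence or two in the protocol or SAP. If the SAP already says this, nothing more is needed.

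**Allocation (optional).** If the number of centres is small, add centre as a REDCap stratum for participants still to be randomised, and keep block sizes varying and undisclosed. This needs a new allocation table and one protocol line. Its downsides are four strata per centre, a few incomplete blocks and somewhat greater predictability of allocation. With many small centres, the analysis change alone is preferable.

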### Analyses

Data will be analyzed (blinded) using intention-to-treat (ITT) principles, including all the data available, regardless of whether the intervention was completed or not. The aims of the ITT analysis are also to provide unbiased comparisons among the two study groups and to avoid the effects of potential study dropouts and protocol deviations. Patients in the intervention group will be compared to patients in the control group.

For the primary outcome, the percentage of patients who have ceased smoking in each group will be calculated and the two groups will be compared using logistic regression. For the dichotomous outcomes and the nominal outcomes, both presented as counts and percentages, Fisher’s exact test and chi-squared test will be used, and the timed dichotomous outcomes will be visualized through Kaplan-Meier plots. In addition, the ordinal outcomes (also presented as counts and percentages) will be analyzed with the Mann-Whitney *U* test. Continuous outcomes will be expressed as means, standard deviations, and interquartile ranges and will be analyzed with *t* tests if normally distributed and Mann-Whitney *U* tests if non-normally distributed. Furthermore, adjusted analyses will be performed with a multivariable Cox proportional hazards model, adjusting for baseline variables and calculating hazard ratio. In addition, the combined outcomes “number of admissions for exacerbations of COPD or death …” and “number of admissions for all causes or death …” will be analyzed in a generalized linear model. Data will be processed and analyzed in SAS with graphs generated therein and in other graph programs such as SPSS.

A Data Safety Monitoring Board, independent from sponsor and competing interests, will monitor the safety of the trial by conducting interim analyzes based on primary and secondary endpoints when half of the study population has completed the study, and thus recommend continuation or termination of the trial.

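### Group sessions and buddy links in the high-intensity arm make clustered outcomes likely, but neither the sample size of 532 nor the named primary logistic regression allows for it

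*Protocol article*

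**What the plan says.** Randomization is individual and 1:1 (Interventions). Beyond varenicline, the high-intensity arm attends group sessions, "in all 30 sessions divided into 6 months", in six phases of five. They are led by a nurse, physician, psychologist, physiotherapist and dietician. The same section adds a buddy scheme: "participants who have completed the program and have become smoke-free are matched with new ones in the program".

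In the Interventions section the low-intensity arm is encouraged to quit through the participant's own GP and receives varenicline. The Abstract and the hypothesis at the end of the Background instead mention a municipal programme or offer, whose format is not described. No section describes trial-run groups for controls.

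The Sample size section sets alpha 5% and power 90%. It assumes for control that "The maximum smoking cessation rate for the “low-intensity group” is expected to be 10% in 12 months" and for the intervention that "≥ 20% of participants are expected to cease tobacco smoking for at least 12 months". It concludes: "This gives a sample size of 532", that is 266 per arm. The increase to 600 is attributed only to withdrawal and loss to follow-up.

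For the primary endpoint the Analyses section says "the two groups will be compared using logistic regression". It mentions no group term, random effect or robust variance.

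**The concern.** Participants who share sessions, staff and peers may succeed or relapse together, and peer support is a deliberate part of this intervention. Buddies add a further link, running from earlier completers to later entrants. On the Interventions text this applies to one arm only, so the design is partially nested: clustered in the high-intensity arm, individual in the low-intensity arm.

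With positive within-group correlation, the quit proportion in the high-intensity arm varies more than a binomial count of the same size. An analysis that ignores this gives confidence intervals that are too narrow and, under the condition set out in the objection, a type I error above 5% on the single primary endpoint. An analysis that allows for it is valid but has less power than the stated 90%.

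**Working it through.** **Inputs from the Sample size section.** Control rate p1 = 0.10, intervention rate p2 = 0.20, alpha 5% (sidedness not stated; two-sided reproduces the figure), power 90%, n = 266 per arm.

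**Inputs not in the document (assumed).** Group size m = 10, with a range of 6 to 20. ICC 0.01 to 0.10.

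**Step 1: reproduce 532.** The pooled mean is p̄ = 0.15. For independent observations,

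n = [1.960·√(2·0.15·0.85) + 1.2816·√(0.10·0.90 + 0.20·0.80)]² / 0.10² = (0.9897 + 0.6408)² / 0.01 = 265.9, so 266 per arm and 532 in total.

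The match is exact, so no design effect is hidden in the figure. Power at 266 per arm is 90.0%.

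**Step 2: design effect, high-intensity arm only.** DE = 1 + (m − 1)·ICC.

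**Step 3: type I error of an unadjusted test under a zero average effect.** The true standard error exceeds the assumed one by √((1 + DE)/2), so the error is 2·[1 − Φ(1.960/√((1 + DE)/2))]. At ICC 0.05, DE = 1 + 9·0.05 = 1.45, √(2.45/2) = 1.107, 1.960/1.107 = 1.771, and the error is 7.7%.

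**Step 4: power at 266 per arm.** Power = Φ[(0.10 − 1.960·SE0)/SE1], with SE1 = √((0.09 + DE·0.16)/266). For a cluster-adjusted test SE0 = √(0.1275·(1 + DE)/266); for an unadjusted test SE0 = √(0.1275·2/266) = 0.0310. At DE 1.45, SE1 = 0.0348.
- Adjusted: SE0 = 0.0343, (0.10 − 0.0672)/0.0348 = 0.94, power 82.7%.
- Unadjusted: (0.10 − 0.0607)/0.0348 = 1.13, power 87.1%.

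**Results for m = 10:**

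| ICC | DE | Type I error, unadjusted | Power at 532, adjusted | Power at 532, unadjusted | Evaluable N for 90%, adjusted |
|---|---|---|---|---|---|
| 0.01 | 1.09 | 5.5% | 88.6% | 89.4% | 560 |
| 0.02 | 1.18 | 6.05% | 87.1% | 88.8% | 586 |
| 0.05 | 1.45 | 7.7% | 82.7% | 87.1% | 666 |
| 0.10 | 1.90 | 10.4% | 75.8% | about 85% | 798 |

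**Step 5: check by simulation.** Beta-binomial group outcomes with Wald logistic tests, 40,000 runs per scenario, gave an unadjusted type I error of about 5.4, 5.8, 7.4 and 9.8% for the four ICCs at a common rate of 10%. The same test gave 4.8% under independence. The formulas are therefore slightly high but sound.

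**Step 6: range.** For m = 6 to 20 and ICC 0.01 to 0.05, adjusted power at 532 runs from 89.2% down to 75.1%, and the evaluable N for 90% runs from 548 to 812.

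**Step 7: does 600 cover it?** The extra 68 participants correspond to a loss of 1 − 532/600 = 11.3%. If nobody were lost, power under independence would be 93.1%, and 90% would hold up to DE of about 1.23, which at m = 10 is an ICC of about 0.23/9 ≈ 0.025. With 532 evaluable, any positive ICC takes adjusted power below 90%.

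**The case against.** A reader might infer that the primary standard errors are wrong as planned and that 90% power is certainly not delivered. The document does not support that, for four reasons.

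- **The analysis is not fully specified.** A mixed or cluster-robust logistic model is still logistic regression. An article may leave the variance estimator to an analysis plan that is not shown. This stands: the standard-error problem is a risk, not a demonstrated error. The sample-size half does not depend on the unseen plan. A plan that adjusted for clustering would make the test valid but could not restore power that the 532 was not sized for.
- **Size depends on two unknowns.** At ICC 0.02 or below with groups of 10, type I error is about 6% or less and unadjusted power about 89%. The endpoint is 7-day abstinence at 12 months, about six months after the last session, so group effects may have faded. This also stands. Nothing in the article supports an ICC as high as 0.10, and nothing rules it out.
- **Type I inflation needs a condition.** Randomization is individual. If the programme affects nobody, forming groups afterwards changes no outcome and the simple comparison stays valid. Inflation arises only if group effects are real but average to zero, with some groups doing better and others worse than control. This stands and limits the claim.
- **Clusters are not cleanly defined.** The article does not say that groups are closed, buddy links cross successive groups, and a municipal programme could itself have a group format. A single design effect is therefore an approximation. That is a reason to record the structure, not to assume independence.

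**Conclusion.** The concern holds in conditional form. The 532 is the independent-observations figure with no allowance for group delivery, and the surplus to 600 is reserved for attrition. The named primary analysis states no allowance either. If within-group ICC is positive and the analysis is unadjusted, standard errors will be too small.

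The practical effect is modest at ICC 0.02 or below and becomes material at about 0.05. There, with 10 per group, type I error is nearer 8% than 5%, and a valid adjusted test has about 83% power at 532 evaluable. These sizes rest on the assumed group size and ICC, on a control arm treated individually, on a simple group-level design effect that ignores buddy links and, for type I error, on group effects that persist when the average effect is zero. The change is worth making because it is cheap and protects the only primary comparison.

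**What to change.** 1. Record for each high-intensity participant the session group (from attendance if groups are rolling) and the buddy link. This may be hard to recover after delivery.
2. Prespecify the primary endpoint analysis as a partially nested logistic model, with a random group effect in the high-intensity arm only, or as logistic regression with cluster-robust variance and each control as a singleton. With 266/10, or about 27, groups, a small-sample correction is advisable for the robust variance.
3. Add a sensitivity analysis for buddy links that cross groups.
4. Reconcile the descriptions of the low-intensity arm, since treating controls as singletons assumes individual care.
5. Restate the power in the Sample size section for a stated group size and ICC range.

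The cost is a few CRF fields, analysis-plan wording and slightly wider intervals. The stated power will fall somewhat below 90% at 532 evaluable. Keeping 90% without more participants is possible only if ICC and attrition are both low; otherwise the sponsor must accept lower power or recruit more.
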